### Phase 2: a feasibility study of the adapted children’s weight management programme

#### Design

The feasibility study will be conducted as a small scale cluster-randomised controlled trial. This will enable estimation of the proportion of families (both Pakistani/Bangladeshi families, and families of other ethnicities) completing the developed intervention programme. It will also provide key information for planning a future effectiveness and cost-effectiveness evaluation of the adapted intervention, including likely recruitment and attrition rates, optimal data collection methods, and parameters to inform a sample size calculation. Programmes delivered across Birmingham within the study period will be randomised to be delivered as either the adapted programme (intervention) or the standard programme (comparator). Families referred to the children’s weight management service will not be aware of the allocation of the programmes and will attend the programme that is most convenient for them.

### Participants

Families in Birmingham with a child age 4–11 years who is overweight (defined as greater than 91st centile for BMI on the UK 1990 growth reference charts [29]) and who are referred to the existing children’s weight management service within the study recruitment period will be eligible to participate. Local service data indicate that 40 % of referrals are Pakistani and Bangladeshi families; however, as the intervention will be adapted primarily to suit Pakistani and Bangladeshi families, we aim to recruit 60 % of participants from these communities and therefore will prioritise recruitment of these families. This will enable us to explore the success of programme adaptation from the perspective of these families. Approximately 800 children and families of all ethnicities are referred to the First Steps programme annually. We aim to recruit 80 children and their families in a 6-month period, and therefore need to recruit 20 % of referred families to participate in the study.

Families referred to the weight management service will initially receive a study invitation letter and information leaflet from the service providers, which will be followed up by a telephone call. If they are interested in participating in the study, they will be contacted by a researcher to arrange a time for an initial home visit to gain consent and collect baseline data. Home visits are anticipated to maximise participation and assist in timely data collection. This data collection process will also allow for blinding of researchers undertaking data collection in a future trial. If a parent/carer requires communication in another language, a person who speaks the relevant language will contact them by telephone to explain the study and invite them to participate, and will complete the initial visit. Written consent will be gained from participating parents/carers, and assent will be gained from children (written if 8 years or more and verbal if under 8 years).

### Study arm allocation

Randomisation of the weight management programmes will be conducted by Birmingham Primary Care Clinical Research and Trials Unit at the beginning of the feasibility study to enable service providers to plan delivery of the programmes. Programme allocation will be concealed from the research team so that they unaware of this at the time of baseline data collection. During the feasibility study period, delivery of 24 programmes across Birmingham is planned. The programmes will be randomised using a 2:1 ratio, so 16 programmes will be the adapted programme and eight will be the standard programme. This will ensure a sufficient number of families in the intervention arm to enable calculation of the primary outcome of completion (see sample size calculation).

### Intervention

Families in the intervention arm will receive the weight management programme for children aged 4–11 years that is developed in phase 1 of the study.

### Comparator arm

Families in the comparator arm will receive the existing First Steps children’s weight management programme (usual care). To avoid contamination between the two arms, the standard and adapted programmes will be delivered by different facilitators.

### Evaluation of the success of intervention adaptation

The primary outcome for the evaluation of programme acceptability and success of its adaptation will be the proportion of Pakistani and Bangladeshi families completing the adapted programme. Proportion of families of all ethnicities completing the adapted programme will also be determined. Completion of the course is defined as attending at least 60 % of the course. This will be assessed using routine attendance data collected at each programme session.

Observations of programme sessions and interviews with the programme facilitators will aim to assess the success of the adaptations in addressing the previously identified barriers and ease of implementation. Each facilitator will be observed delivering all sessions at least once across the study intervention period. Members of the research team will undertake observations and will make notes on the delivery of and response to the session. Additionally, in depth interviews will be undertaken with parents/carers who attend the adapted programme to explore their experiences of the programme, barriers and facilitators to engagement and their views on its structure, delivery and content. Approximately 15–20 interviews will be undertaken (approximately half with Pakistani and Bangladeshi parents and half with parents of other ethnicities). We will purposively sample to include parents who completed the programme and those who only partially attended. Interview schedules will be developed to include prompts on the specific adaptations made during the programme development process. The interviews will be undertaken by either the core research team or Community Researchers in the participants’ preferred languages. The interviews will be audio-recorded, translated and transcribed verbatim. Views of children completing the adapted programme will also be sought. Approximately ten children aged 8 years or over (five Pakistani/Bangladeshi and five of other ethnicities) will be recruited to participate in interviews to explore their experiences and engagement with the programme, using appropriate interview techniques for this age group. Written consent and assent will be gained from facilitators, parents and children for participation in the interviews.

### Outcome measures for use in a future trial to evaluate programme clinical and cost-effectiveness

A range of other outcome measures will be assessed for feasibility and thus inform design of a definitive effectiveness and cost-effectiveness evaluation. Child measures will include measures of adiposity, assessment of pubertal status, usual eating patterns, objectively measured physical activity, psychosocial measures and a quality of life utility measure. Measures with parents and other family members will include adiposity measures, assessment of family eating and physical activity behaviours, parenting styles, parental feeding practices and parental self-efficacy. Further details of these assessments are shown in Table 2.

**Table 2 Tab2:** Outcome measures on children, parents and other family measures in the phase 2 feasibility study

Measures of adiposity	
•	Height and weight - to calculate BMI z-score
•	Waist circumference
•	Percentage body fat - derived from bioimpedance analysis
Pubertal assessment	
•	In girls aged > 8 years - visual assessment of breast development (child clothed): a modified approach to the Tanner breast development scoring system [44], and history of menarche obtained
•	In boys - assessment of facial hair growth
Usual eating patterns	
•	Children’s Dietary Questionnaire administered to parents/carers [45] - adapted for use in the local population
Objectively measured physical activity	
•	Geneactiv (wrist) or Actigraph (hip) worn for 7 days
Psychosocial dimensions	
•	Health-related quality of life - assessed using Pediatric Quality of Life Inventory [46]
•	Body image - assessed using the Figure Rating Scale [47] (adapted for use in the local population)
Quality of life utility measure for use in economic evaluation	
•	Child Health Utility 9D (CHU 9D) [48]
Parent/carer and family assessments	
•	Height, weight and bioimpedance of parents/carers and other family members - to calculate BMI and percentage body fat
•	Parent/carer feeding practices - assessed using the Comprehensive Feeding Practices Questionnaire [49]
•	Parenting style - assessed using the Parenting Styles and Dimensions Questionnaire [50]
•	Parental self-efficacy - assessed using the Parental Locus of Control Scale [51]
•	Family food and physical activity behaviours - assessed using the Family Nutrition and Physical Activity screening tool [52]

### Sociodemographic information

Age, sex, and ethnicity of the child, family migration history, religious beliefs/practices, home postcode (to be mapped to Index of Multiple Deprivation scores), parent/carer occupation, and parent/carer education level will be collected from parents/carers at the baseline home visit.

### Outcome data collection procedure

Physical measurements and other assessments will be undertaken on children and parents/carers at three time points: baseline, post-intervention and 6 months post-intervention. Trained research staff will undertake data collection in the participant’s home, or at another location convenient to the participant’s family. For the questionnaire-based data collection researchers will verbally administer questionnaires directly to children. Parents can choose to self-complete or verbally complete questionnaires with the researcher. If the participant’s preferred language is not English, trained Community Researchers will administer the questionnaires and undertake other data collection using the relevant language. Researchers and families will be blind to their treatment allocation at the time of baseline measures. The feasibility of this data collection approach will be assessed to inform a future trial.

### Cost data to inform a future economic evaluation

Methods for collecting data on direct intervention costs and costs from a societal perspective will be developed and tested during the feasibility study. Specifically we will include items such as parent/carer productivity costs (time off work to attend the intervention sessions), associated childcare costs and changes to the weekly food bill.

### Process evaluation

We will develop process evaluation methods to inform a future trial, in accordance with the UK MRC guidance on process evaluation of complex interventions [39]. The planned interviews with parents/carers attending the programme, direct observation of programme delivery, and interviews with programme facilitators will enable assessment of various aspects of implementation, mechanisms of impact and contextual factors influencing intervention delivery and how the intervention is received. Specifically, direct observation and interviews with facilitators will enable assessment of dose and fidelity of delivery, and direct observation and interviews with parents and children will enable assessment of participant response, unanticipated pathways and contextual influences.

### Sample size

To calculate the primary outcome (the proportion of Pakistani and Bangladeshi families completing the adapted programme), we will use anonymised data on completion that is routinely collected by the children’s weight management service. From existing service data, the mean group size at the start of a programme is 11. Therefore, we expect approximately 176 families to start attending the 16 adapted programmes delivered in the intervention period, 40 % of which will be Pakistani or Bangladeshi (i.e. approximately four to five Pakistani and Bangladeshi families will start attending each of the adapted programmes within the study period, 70 families in total). This will allow an estimation of the proportion of Pakistani and Bangladeshi families completing the programme to within 26 % precision. For example, if 65 % of Pakistani and Bangladeshi families complete the adapted programme, the 95 % confidence interval of the estimate of completion will be 52–78 %. To estimate this confidence interval, we have inflated the variance we would expect under individual randomisation by the typical variance inflation factor for cluster trials (with an additional inflation of 11 % to account for the varying cluster size [40]). We have assumed a mean cluster size of 5. There is no specific data to inform the estimate of the intra cluster correlation co-efficient (ICC), therefore, using current recommendations we have drawn on patterns of ICCs from other sources [41]. Our outcome is a process outcome; our clusters are small; and the prevalence of our outcome (completion) is expected to be moderate. The latter is associated with generally lower ICCs whereas the two former are generally associated with higher ICCs. We therefore have assumed a moderate ICC of 0.05 [42].

To test recruitment and data collection methods and gain an estimate of recruitment and attrition rates to inform a future trial, we plan to recruit at least 80 children and families into the study. This number of participants will also enable estimation of the key parameters required for a sample size calculation of a future trial [43].

### Data analysis

The proportion of Pakistani and Bangladeshi families completing the adapted intervention programme and 95 % confidence intervals will be calculated using routinely collected service data. Secondary analyses will include estimation of the proportion of all families completing the adapted programme and 95 % confidence intervals, and a comparison of proportion of families completing the programme in the intervention and comparator arms (using intention to treat analysis). Confidence intervals will be estimated from the appropriate mixed-effects model to allow for the clustered nature of the data.

To provide information on the feasibility of outcome measures, we will report the number of measurements attempted for each outcome and the proportion of complete assessments made. To provide sample size calculation parameters for a future trial to assess intervention effectiveness, feasible outcome measures will be reported using the appropriate summary statistics and correlations between baseline and follow-up will be estimated for continuous outcomes.

Although the study is not sufficiently powered to detect minimum clinical differences in adiposity outcomes between intervention and comparator arms, estimates of differences in these and other outcomes between arms will be calculated. Mixed-effects models will be developed, adjusting for clustering and baseline measures, and 95 % confidence intervals will be reported and differences deemed significant at the 5 % level. This model will also provide an estimate of the ICC and 95 % confidence interval for use in a sample size calculation for a future trial to evaluate effectiveness.

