A need for direct comparisons between existing health promotion programmes and those that are adapted for minority ethnic groups has been highlighted [21]. Phase 2 of this study directly compares the adapted programme to the standard programme, and evaluates the success of programme adaptation through several methodologies. The feasibility study also enables further refinement of the adapted programme and allows us to gather information to inform a trial evaluating programme effectiveness. This study will provide important information on both the feasibility of recruitment in a culturally and ethnically diverse population, and likely attrition rates in a trial. The process of home visits for data collection is a particular strength of the study design as it is likely to minimise attrition. A range of outcome measures that relate to the intervention are being tested in the feasibility study. This will enable identification of the primary outcome measure and important secondary outcome measures for inclusion in a future trial to evaluate programme effectiveness. We recognise that multiple outcome measures may overburden participants, and the feasibility study gives us the opportunity to assess this and prioritise which outcome measures to include in a future trial. The feasibility study also provides the opportunity to develop rigorous methodology for process and cost-effectiveness evaluation for use in a future trial. These are key areas to address in the definitive evaluation of complex interventions [27, 28].

The decision to undertake a full scale trial to evaluate clinical and cost-effectiveness of the adapted programme will primarily depend on the success of the programme at increasing family completion rates, and the acceptability of the programme to families from all cultural backgrounds. If we progress to a full trial, the valuable information gained on the feasibility of study design, processes and data collection will shape trial design and inform a sample size calculation.

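### A 5% significance rule is attached to an open-ended set of between-arm differences in a feasibility study that disclaims power for adiposity and states none for the rest

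*Protocol article*

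**What the plan says.** The protocol article's Data analysis section concedes that "the study is not sufficiently powered to detect minimum clinical differences in adiposity outcomes between intervention and comparator arms". The same sentence goes on to say that "estimates of differences in these and other outcomes between arms will be calculated". Mixed-effects models are to adjust for clustering and baseline, and 95% "confidence intervals will be reported and differences deemed significant at the" 5% level.

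The outcomes are those of Table 2, introduced with "A range of other outcome measures will be assessed for feasibility and thus inform design of a definitive effectiveness and cost-effectiveness evaluation". They are measured "at three time points: baseline, post-intervention and 6 months post-intervention". The sample is set in Sample size: "we plan to recruit at least 80 children and families into the study". Study arm allocation randomises programmes 2:1, 16 adapted and 8 standard.

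Study aims and objectives lists feasibility, completion, acceptability and parameters for a future trial. It contains no objective to test effects on adiposity, behaviour or psychosocial outcomes.

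**The concern.** A significance threshold turns an estimate into a verdict. Here it covers comparisons for which the authors either concede inadequate power (adiposity) or give no power at all (everything else), and it answers no stated objective. The quantities that the section wants for a future trial are summary statistics, baseline to follow-up correlations and the ICC with its interval. None of these needs a threshold.

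Two misreadings are at stake. With many comparisons, some results will probably be labelled significant by chance. In a sample this small, a difference has to be large to earn the label, so labelled estimates will tend to overstate the truth. A reader could take either as evidence that the adapted programme works, and a planner could carry an inflated difference into the next sample size calculation.

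**Working it through.** **The plan's own figure.** The only computed precision in the article is for completion: 65% of 70 families, mean cluster size 5, ICC 0.05, extra inflation 11%.
- Design effect = [1 + (5 − 1) × 0.05] × 1.11 = 1.332.
- Half-width = 1.96 × √(0.65 × 0.35 / 70 × 1.332) = 0.129.
- Interval = 52.1% to 77.9%, which reproduces the stated 52–78%.

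There is no corresponding figure for the between-arm differences.

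**Number of comparisons.** The article does not fix it. My count of Table 2 is 14:
- 8 child outcomes: BMI z-score, waist, body fat, diet, physical activity, health-related quality of life, body image, utility.
- 6 parent or family outcomes: BMI, body fat and four questionnaires.

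Pubertal assessment and subscales are left out. Testing both follow-ups separately would give 28.

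**Chance of a false positive**, all nulls true and tests independent: 1 − 0.95^k, with 0.05 × k expected.

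| Tests | Expected false positives | Chance of at least one |
|---|---|---|
| 14 | 0.7 | 1 − 0.95^14 = 51% |
| 28 | 1.4 | 1 − 0.95^28 = 76% |

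Positive correlation, certain among adiposity measures on the same child, lowers the last column but not the expected number.

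**Size of difference needed for significance.** Assumptions: 80 families split about 53 to 27, spread evenly over 24 programmes (80/24 = 3.33 each), no attrition, no baseline adjustment, and an ICC of 0.05 borrowed from the completion outcome.
- Design effect = 1 + (3.33 − 1) × 0.05 = 1.117.
- SE = √[1.117 × (1/53 + 1/27)] = 0.25 SD.
- Significant only if the estimate is at least 1.96 × 0.25 = 0.49 SD.
- 80% power needs 2.80 × 0.25 = 0.70 SD.

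**Effect of the planned baseline adjustment.** The SD shrinks by √(1 − r²). The article gives no r. For an assumed 0.7 to 0.9 the factor is 0.71 to 0.44, so the significance threshold falls to about 0.35 to 0.21 SD and the 80% power difference to about 0.5 to 0.3 SD. Attrition pushes both back up.

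**Against the article's own benchmark.** The Background cites BMI z-score effects of 0.06 (preadolescents) and 0.14 (adolescents) against standard care. It gives no SD, so I assume 0.2 to 0.6 for the quantity analysed, after any baseline adjustment.
- The threshold of 0.49 SD is then 0.10 to 0.29 in BMI z-score. A significant favourable estimate would be at least 1.6 to 4.9 times a true 0.06.
- Power with the design effect is 22% down to 6% for 0.06, and 80% down to 15% for 0.14.

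**The case against.** The strongest reply is that nothing in the plan depends on these verdicts. The Discussion ties the decision on a full trial primarily to completion and acceptability. Data analysis judges the measures by numbers attempted and proportions complete, and lists no observed effect size among the sample size parameters. This stands. A reader might infer from the Discussion's "This will enable identification of the primary outcome measure and important secondary outcome measures for inclusion in a future trial" that chance findings will decide what goes into the next trial. The sentence does not say so: it refers to the testing of a range of measures, and what follows concerns participant burden. The Discussion gives no explicit selection rule, so influence is possible, but it is not planned.

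Three further points stand in part.
- The power concession covers adiposity only. It would be wrong to say that the paragraph disclaims power for every outcome; for the others it is silent.
- The count of 28 and the independence assumption are mine, and the 0.49 and 0.70 SD figures ignore the planned baseline adjustment. They are indications of size, not properties of the planned analysis.
- Multiplicity handling or an exploratory label may sit in an analysis plan that is not shown. Their absence here is therefore not the defect. The defect is the rule that the article does state.

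It is also fair that the paragraph warns of low power and promises intervals, which limits the risk that a non-significant result is read as no effect. Nor can one say that most significant results would be false, since that depends on how many nulls are true.

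**Conclusion.** The point holds in a limited form. The article attaches a 5% significance verdict to an open-ended set of comparisons that no objective calls for, directly after conceding inadequate power for the adiposity ones. The 51% to 76% chance of at least one false positive is for 14 to 28 independent tests with all nulls true, and is lower under correlation. The exaggeration is real in direction, but its size depends on the unknown SD, baseline correlation, ICC and attrition.

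The consequence is that readers and planners could be misled about efficacy. The stronger inference, that significance will determine progression, outcome choice or the future effect size, is not supported. The primary estimate of completion, its interval and the sample size are unaffected.

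**What to change.** In the last paragraph of Data analysis, delete the clause that deems differences significant at the 5% level. Keep the adjusted differences with 95% confidence intervals and label them descriptive or exploratory. Add one sentence saying that they support no efficacy conclusion and will be used neither to select outcomes nor to set the effect size for the future trial.

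The cost is one deleted clause and one added sentence. No data, model, estimate or sample size changes.
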